**Fig. 5 Fig5:**
[figure not shown]
SNAPE lifestyle survey reportEDS development, use and reporting protocolOnce partner sites were identified, we identified the CARPA standard treatment manual as the most appropriate guideline for CVD and diabetes EDS development. As Communicare is the EHR system used by all partner sites, ideally the TEAMSnet EDS application would need to be interfaced with Communicare for automated syncing of as much of the clinical data required by EDS as possible so as to avoid duplication and improve clinical efficiency. The developers of the CARPA standard treatment manual and Communicare were advised of the TEAMSnet project and agreed to support the project informally as advisors and collaborators, particularly in relation to timing of their product updates and releases. In return, TEAMSnet would provide both organisations with potentially useful user feedback during the project.TEAMSnet EDS will provide clinicians with three CVD and diabetes management tools.The **CVD risk calculator and slide rule** that enables baseline measurement and regular monitoring of a participant’s overall CVD risk (Fig. 6).The **detailed CVD and diabetes risk-analysis tool** that provides a clinician with specific recommendations and optional learning points for best-practice management of a participant’s CVD risk (Fig. 7).
**Active CVD and diabetes decision-support tool** — a proactive clinical process whereby each recommendation is reviewed by the clinician and either accepted or rejected, in which case a textbox appears for the explanation. An EDS report will be generated for each participant as soon as possible after the second clinical visit [at which surveys are administered]. A second and final EDS report will be generated for participants prior to the end of the study (Fig. 8).

**Fig. 6 Fig6:**
[figure not shown]
CARPA-designated risk analysis inputs

**Fig. 7 Fig7:**
[figure not shown]
CARPA-based risk analysis report

**Fig. 8 Fig8:**
[figure not shown]
CARPA-based EDS report with accepted and rejected risk analysis recommendationsMobile tablet applicationMobile tablet development and use will enable display and review of much of the data derived from GRI, SNAPE surveys and EDS applications. Surveys can be administered and an educational resource library can be populated and accessed via the tablet, and this can take place in an out-of-clinic setting, thereby facilitating patient engagement.

### Data collection and outcome measures

Demographic data (including age, gender, postcode, contact details) and self-report measures are obtained from each participant at baseline and/or at the 6-month survey administration visit. Pre- and post-study clinical data such as blood and urine biochemistry, blood pressure and anthropometric measures including height and weight are also collected. Pre- and post-study health care resource utilization is captured through EHR records and includes information on hospitalizations and eye-care consultations.

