Our second objective is to improve the timely exchange of relevant health information and the communication between a patient’s health care providers. CDMP facilitates this through use of a unique practitioner access code that enables a specialist medical practitioner, such as an optometrist or ophthalmologist, to view only relevant patient data, including reports.
*Improve engagement of patients in self-care, particularly adherence to clinical visits*
Our third objective is to improve engagement of patients in self-care. GRI retinal imaging will provide both a powerful education and retinopathy assessment opportunity. In addition, a third technology, (3) a custom-built e-mobile health device in the form of a tablet with viewable clinical data, GRI images and educational content, developed with clinical and Aboriginal Health Worker input, will facilitate health worker communication with patients between medical consultations and is aimed at improving relationships and engaging patients in self-care. A fourth application, (4) a suite of lifestyle surveys and a related reporting template based on CARPA recommendations for smoking, nutrition, alcohol, physical activity and emotional well-being [SNAPE] has been developed and is accessible via CDMP in a clinical setting or via the mobile tablet application anywhere. This is designed to be both a patient engagement and clinical management tool that facilitates the measurement, goal-setting and monitoring of important lifestyle risk factors for CVD, diabetes and diabetic retinopathy. All three telehealth reports, EDS, GRI and SNAPE, will be accessible via either the EHR [Communicare] or CDMP.

Apart from the development and implementation of the four technologies, the primary outcome includes improved adherence to clinical care, such as eyecare visits. Secondary outcomes include reduction in hospitalizations and cost-efficacy of the suite of technologies, both individually and collectively.

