#### Exclusion criteria

Clients of the partner health services are ineligible if they been clients for less than six months prior to enrollment or have had diabetic retinopathy treatment.

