#### Pre-study data

Site partners will collaborate to audit the Communicare EHR for each participant in order to obtain the required pre-study data i.e. the data that correspond with post-study data relating to CVD, diabetes or diabetic retinopathy risk and outcomes and each participant’s use of health services, such as eye-care consultations and hospitalizations.

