## Sample Size

For a conservative differential in adherence to subsequent care of 15%, and with 80% power, the minimum sample required is 490. Estimates are based on a 25% attrition rate. We will therefore need 600 participants across the three partner sites.

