## Data analysis

Investigators and their supporting statistics departments will conduct data analysis. Site differences will be analysed. Analyses will provide important descriptive data, such as prevalence rates and lifestyle data, proportion treated to target for CVD, diabetes and diabetic retinopathy risk factors and predictors of diabetic retinopathy and CVD outcomes. Analysis of covariance (ANCOVA) will be used to compare differences between groups. To assess confounding, covariates will include age, gender, and established and emerging risk factors for CVD, diabetes and diabetic retinopathy, as appropriate. Non-parametric statistics will be used when assumptions for parametric methods are violated. All tests will be conducted using an alpha level of 0.05 and 95% confidence intervals will be reported.

Complete case analysis and, where reasonable, multiple imputation will be employed for the management of missing data. Missing data may occur due to drop-out, missed assessments or item non-response. With knowledge of the missing data mechanism, all available information can be used. One approach will be to use the multilevel model, a full-likelihood method that allows for a response to be missing at random, where missingness depends only on observed data and not on unobserved data. Another strategy involves imputing missing values by multiple imputation procedures.

The proposed economic evaluation aims to include pre- and post-study resource utilization costs for both the costs and consequences and a cost consequence analysis (CCA). Standard unit costs i.e. Australian Medicare Benefits Schedule will be applied to the resource-use data. Costs will be presented in total and disaggregated forms, such as those from different sectors — the health sector, patients and government.

Of the recruitment target of 600 Indigenous Australians with diabetes, to date 576 participants have been recruited and undergone retinal imaging for diabetic retinopathy screening.

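### Hospitalisations come from EHR records in an uncontrolled pre-post study; those records cannot by themselves separate no admission from no longer observed, so a spurious fall can arise

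*Protocol article*

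**What the plan says.** On the outcome, Study aims and objectives states: "Secondary outcomes include reduction in hospitalizations and cost-efficacy of the suite of technologies, both individually and collectively".

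On the source, Data collection and outcome measures states: "Pre- and post-study health care resource utilization is captured through EHR records and includes information on hospitalizations and eye-care consultations". For the period before the study, the Pre-study data section adds: "Site partners will collaborate to audit the Communicare EHR for each participant in order to obtain the required pre-study data". It says that these data are to correspond with the post-study data. The text on decision-support development in Study procedure identifies whose system this is: "As Communicare is the EHR system used by all partner sites". The article mentions no other source, such as hospital or death records.

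On who is observed, the Exclusion criteria make clients "ineligible if they been clients for less than six months prior to enrollment". After enrolment, the Inclusion criteria ask only for willingness to see a doctor at least twice over 18 months. The Sample Size section states: "Estimates are based on a 25% attrition rate".

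On analysis, Data analysis states: "Complete case analysis and, where reasonable, multiple imputation will be employed for the management of missing data". It names drop-out, missed assessments and item non-response as causes of missing data, and offers a multilevel model valid under missing at random. The economic evaluation applies Medicare unit costs to the resource-use data. Study design describes a pre-post study and no concurrent control.

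**The concern.** The two periods are not observed alike. Just before baseline every participant is alive and has been known to the service for at least six months. Afterwards people can die, move or change service. A blood pressure that was not taken is visibly missing. A hospital admission that never reached the service's record is simply an absent entry, and so is an admission that never happened.

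The missing-data methods in Data analysis work only on values recognised as missing. If departures are not identified, none of those methods is triggered. If they are identified, complete-case analysis removes the people who died or left. Should admissions run higher before death, this removes high post-period use and keeps stable survivors.

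With no concurrent control, loss of observation cannot cancel between groups. A reported fall in admissions, and a saving calculated from it, could partly reflect lost observation.

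**Working it through.** The article gives no figure for hospitalisations or costs, so there is nothing of its own to reproduce. Its sample size concerns adherence and does not bear on this point.

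**Inputs from the article:** 600 participants; 25% attrition, so 600 × 0.25 = 150 people; at least six months as a client before enrolment.

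**Assumptions not in the article:** pre and post windows of 18 months each; a constant true admission rate; no effect of the intervention; time after departure read as zero use; departure unrelated to admission risk.

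**Step 1. Pre window fully observed.** Let *a* be the share who leave the record and *f* the mean fraction of the post window observed for them. Then

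apparent rate ratio = 1 − a(1 − f).

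Planned post-period person-time is 600 × 1.5 = 900 person-years.

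| Scenario | Person-years lost | Apparent rate ratio |
|---|---|---|
| One third of attrition (50 people) leaves, evenly spread | 50 × 0.75 = 37.5 | 862.5/900 = 0.958 |
| All 150 leave, evenly spread | 150 × 0.75 = 112.5 | 787.5/900 = 0.875 |
| All 150 leave at 6 months | 150 × 1.0 = 150 | 750/900 = 0.833 |
| All 150 leave at baseline | 150 × 1.5 = 225 | 675/900 = 0.750 |

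**Step 2. Pre window partly unobserved.** Let *b* be the share of participants whose pre window is incomplete and *g* the mean fraction observed for them. Then

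apparent rate ratio = [1 − a(1 − f)] / [1 − b(1 − g)].

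Only 6 of 18 months is guaranteed, so *g* can be as low as 1/3. At that extreme the two losses cancel when b = a(1 − f)/(2/3):

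- one third of attrition leaving, evenly spread: (37.5/900)/(2/3) = 6.25% of participants;
- all attrition leaving, evenly spread: 0.125/(2/3) = 18.75% of participants.

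The net direction therefore depends on client tenure and on the length of the look-back. The article gives neither.

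**Step 3. Effect on the test.** A simulation under no effect used 600 participants, 1,000 runs per setting, gamma-Poisson counts (shape 0.5 to 1), fully observed 18-month pre windows and an assumed 0.3 to 1.0 admissions per person-year. With post-departure time read as zero, the probability of a significant false decrease, against a nominal 2.5%, was:

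- 7–17% with 10% loss, evenly spread;
- 29–75% with 25% loss, evenly spread;
- 82–100% with 25% loss at enrolment.

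Analysing observed person-time, or only those still under observation, brought the two-sided error back to about 4–6%. That holds only because departure was simulated as unrelated to admission risk. The simulation does not quantify the complete-case bias when those who die or leave differ in risk.

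**The case against.** The strongest reply is that the harm needs a rule the article never states. A reader might infer that leavers will be counted as having no admissions, and that a fall of 12.5% to 25% will follow. The documents do not support that reading:

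- No passage says that absent records count as zero. Data analysis lists drop-out as missing data.
- The 25% attrition belongs to a sample size for adherence and is not defined as death or leaving the service. Someone who misses a survey but remains a client still generates record entries.
- The pre window has no stated length and may itself be under-observed beyond six months, which works against an apparent reduction.
- Under the zero reading, admissions shortly before death would be in the record if they reached it, and would offset some of the lost time.
- Costs are not read from the record. They are unit costs applied to resource use, so they can only inherit a bias.
- Communicare is named as the audited source only for pre-study data.

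All of this stands, and it limits the claim to what can arise. It does not remove the point. An empty record does not declare itself missing, and the article names no means of identifying departures.

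It can also be said that windows and censoring rules belong in a full protocol or analysis plan that is not shown. That is fair for the rules themselves. The data source and the complete-case approach, however, are stated here, and an analysis plan can apply censoring only if the necessary dates are extracted.

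**Conclusion.** The point holds in a conditional form. The stated source, an uncontrolled pre-post comparison and a complete-case approach together leave the hospitalisation outcome, and costs derived from resource use, open to a spurious fall.

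The illustrative rate ratios of 0.96, 0.875 and, at worst, 0.75 rest on equal and fully observed 18-month windows, no true effect and absent records read as zero. They are not predictions. Incomplete observation before enrolment could offset part or all of the fall, so the net direction is not assured. The bias from dropping those who die or leave cannot be sized, because the article gives no death or admission rates.

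This affects a secondary outcome and the economic evaluation. It is worth acting on because the improvement is cheap.

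**What to change.** 1. In the EHR audit, extract each participant's client start date, transfer or inactive status with its date, and date of death where recorded.
2. Define observed time for each participant in both the pre and post windows. Start the pre window no earlier than the client start date. End the post window at the earliest of death, recorded transfer or inactive status, and the end of the window.
3. Keep everyone in the analysis. Compare hospitalisation and resource-use rates per observed person-year, using a log person-time offset, in place of complete cases. Report costs per observed person-year.
4. Report deaths and departures by site beside the result, and add a sensitivity analysis for hospitalisation or death. This is needed because person-time alone does not correct for departure or death that is related to admission risk.

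The cost is a few added fields in an audit already planned, plus analysis wording. Data analysis reports 576 of 600 participants recruited and the audit is described as still to come, so the fields should be settled now. The article does not say that these status dates are held in the record. They may be imprecise or absent for some participants, and the apparent reduction may become less favourable.

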#### Pre-study data

Site partners will collaborate to audit the Communicare EHR for each participant in order to obtain the required pre-study data i.e. the data that correspond with post-study data relating to CVD, diabetes or diabetic retinopathy risk and outcomes and each participant’s use of health services, such as eye-care consultations and hospitalizations.

### Data management

The study coordinators at respective sites will be responsible for electronic scanning and storage of hard copies of participant consent and report forms for entry into the password protected central database. Hard copies will be kept in a secure cabinet at the respective sites. If requested, participants can access their individual results at study completion.

### Study integrity

Approval to conduct the study was received from Central Australian and Menzies School of Health Research Human Research Ethics Committees in the Northern Territory. Written informed consent will be obtained from all participants. A local translator will assist in consenting patients for whom English is not their first language.

## Sample Size

For a conservative differential in adherence to subsequent care of 15%, and with 80% power, the minimum sample required is 490. Estimates are based on a 25% attrition rate. We will therefore need 600 participants across the three partner sites.

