**Methods:**

Using a pre-post intervention design, 600 Indigenous Australians with type 2 diabetes will be recruited from three primary-care health-services in the Northern Territory. Diabetes status will be based on clinical records. There will be four technological interventions: 1. Baseline retinal imaging [as a real-time patient education/engagement tool and telehealth screening strategy]. 2. A lifestyle survey tool administered at ≈ 6-months. 3. At ≈ 6— and 18-months, an electronic cardiovascular disease and diabetes decision-support tool based on current guidelines in the Standard Treatment Manual of the Central Australian Rural Practitioner’s Association to generate clinical recommendations. 4. Mobile tablet technology developed to enhance participant engagement in self-management. Data will include: Pre-intervention clinical and encounter-history data, baseline retinopathy status, decision-support and survey data/opportunistic mobile tablet encounter data. The primary outcome is increased participant adherence to clinical appointments, a marker of engagement and self-management. A cost-benefit analysis will be performed.

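### The sample-size figures of 490 required, 25% attrition and 600 enrolled do not reconcile, so the stated 80% power does not describe the planned study on either reading of 490

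*Protocol article*

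**What the plan says.** The whole sample-size justification is one short paragraph in the Sample Size section of the protocol article. It names the effect ("For a conservative differential in adherence to subsequent care of 15" per cent), sets power at 80%, and concludes that "the minimum sample required is 490. Estimates are based on a 25% attrition rate. We will therefore need 600 participants", to be spread over the three sites.

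The paragraph does not say whether 490 counts people analysed or people enrolled. The significance level is in the Data analysis section: "All tests will be conducted using an alpha level of 0.05", without sidedness. The Abstract describes the design: "Using a pre-post intervention design, 600 Indigenous Australians with type 2 diabetes will be recruited". The Data analysis section also reports that "to date 576 participants have been recruited and undergone retinal imaging for diabetic retinopathy screening", so enrolment was close to its target when the article was written.

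**The concern.** The word *therefore* presents 600 as the result of allowing for 25% loss on top of 490. Anyone who repeats that step gets a different number. The alternative, that 490 already contains the allowance, does not produce 600 either.

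The paragraph supports the primary outcome, adherence to clinical appointments, and the target of 600 is repeated in the Abstract, in Study design and in Data analysis. A null result on adherence will be read against the stated 80%. If that figure belongs to a sample other than the one planned, the reader cannot tell how much weight a null result can bear.

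**Working it through.** **Inputs.** From Sample Size: difference 15%, power 80%, minimum 490, attrition 25%, target 600. From Data analysis: alpha 0.05. Assumed because not stated: two-sided testing, an absolute 15-point difference unless noted, and a range of baseline adherence rates.

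**Step 1: try to reproduce 600 from 490 and 25%.**
- Standard inflation, N/(1 − d): 490/0.75 = 653.3, so 654. Not 600.
- Common mistake, N × (1 + d): 490 × 1.25 = 612.5, so 613. Near 600, but not equal to it.
- Forward check: 600 × 0.75 = 450 completers, and 490 − 450 = 40 short.
- Attrition at which 600 leaves 490: 1 − 490/600 = 18.3%.

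**Step 2: read 490 as already inflated.** Completers needed: 490 × 0.75 = 367.5, so 368. The enrolment figure is then 490 itself, and the further 600 − 490 = 110 participants have no stated source.

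**Step 3: power for 450 completers.** If n0 completers give exactly 80% at two-sided 0.05, power at n is approximately Φ(2.8016 × √(n/n0) − 1.96), where 2.8016 = 1.96 + 0.8416.
- n0 = 490: Φ(2.8016 × √(450/490) − 1.96) = Φ(0.725) = 76.6%.
- n0 = 367.5: Φ(2.8016 × √(450/367.5) − 1.96) = Φ(1.140) = 87.3%.

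Against the stated 80%, these differ by about −3 and +7 points.

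**Step 4: which reading of 490 do standard formulas support?**
- *Two equal independent groups, absolute 15 points, baselines 10% to 80%:* the largest total is 348, or 374 with continuity correction, both at a baseline of 42.5%. So 490 is not reproduced as an analysed number.
- *Same formula, continuity-corrected, divided by 0.75:* totals of 366 to 374 at baselines 35% to 50% give 488 to 499. So 490 is reproduced as an already inflated number at some of these assumed baselines.
- *Paired pre-post (McNemar) approximation,* n = (1.96√ψ + 0.8416√(ψ − 0.15²))²/0.15², with ψ the proportion of discordant pairs: even at ψ = 1, n = 347.
- *Power with 450 for an absolute 15 points:* at least 89% as two groups of 225 at every baseline tried, and 89% (ψ = 1) to over 99% (ψ = 0.2) as 450 pairs.
- *Relative 15%, two groups:* 528 in total at a 70% baseline, rising to 2,136 at 40%. 490 is not reproduced at the baselines tried, and each of these totals exceeds 450.

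**The case against.** A reader might infer from Step 1 that the study is underpowered. The documents do not support that as a flat statement. The 76.6% needs two things to be true: that 490 is a completer count, and that 490 completers give exactly 80%. The article states neither. The sentence on attrition comes directly after 490 and can be read as saying that 490 already includes the allowance. Step 4 favours that reading for an absolute 15-point difference, and on it 600 is simply a target above the minimum. The simple formulas put power at 450 at 89% or more. This objection stands. A relative 15% or clustering by site could reverse it, but the article mentions neither as a basis for the calculation.

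A reader might also apply 25% loss to the 576 recruited and quote a still lower power. That is not warranted, because 576 is a count to date against a target of 600 and not the final sample.

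Finally, loss from study visits need not mean loss from the primary comparison. Data collection and outcome measures, with Pre-study data, takes service use, including eye-care consultations, from electronic health records. Data analysis also plans multiple imputation and a full-likelihood multilevel model. This stands too: 450 is the number implied by the stated attrition, and not necessarily the number analysed.

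None of this makes the printed step correct. If 490 is before attrition, 600 is too small for it. If 490 is after attrition, *therefore* has nothing behind it. Nor is this detail that an article leaves to a fuller document, because all three figures and the inference joining them are printed.

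**Conclusion.** The point holds as an unreconciled derivation. As a completer count, 490 calls for 654 enrolled, which is 54 more than the target, and 600 leaves 450, which is 40 below the stated minimum. As an enrolment count, 490 implies about 368 completers and leaves 600 unexplained. In neither case is 80% the power of 600 enrolled with 25% loss: it is about 77% on the first reading and about 87% on the second, given two-sided 0.05 and exactly 80% at the relevant base number.

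The attrition arithmetic does not depend on the test behind 490. The power figures do depend on these assumptions, and even the direction of the error is open. A shortfall is possible but not shown, and on the less favourable reading it is about 3 points.

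**What to change.** Do not enrol more participants. Correct the paragraph as follows:

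1. State whether 490 is the number analysed or the number enrolled.
2. Correct the inflation step, or give the actual reason for 600.
3. Restate power for the 450 expected completers, recomputed from the sponsor's own baseline adherence rate and pre-post formula, and say whether 15% is absolute or relative.

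Until that recomputation is done, the wording could be one of these:
- If 490 is completers: *600 enrolled with 25% attrition leaves 450, with power of about 77% for the 15% differential; 80% holds only if attrition is at most about 18%.*
- If 490 is enrolled: *about 368 completers are required; 600 enrolled with 25% attrition leaves 450, with power of about 87%.*

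Carry the corrected figure into the interpretation of the primary result. The cost is a sentence or two and one recalculation, with no change to study procedures. The stated power may come out slightly lower than 80%, or higher.

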## Methods/Design

### Study design

This is a pre-post study of technology-facilitated management of diabetes, CVD, and diabetic retinopathy. We plan to enrol 600 adults (age ≥18 years) with clinically-diagnosed diabetes from three remote Northern Territory Aboriginal-controlled health services — Central Australian Aboriginal Congress [CAAC] in Alice Springs, Miwatj Health Aboriginal Corporation [Miwatj] that incorporates the four clinics at Nhulunbuy, Galiwin’ku/Elcho Island, Yirrkala, Gunyangara/Ski Beach in East Arnhem Land and Wurli-Wurlinjang Health Service [Wurli] in Katherine. Recruitment and intervention are anticipated to occur over a 3-year period. Participants will receive retinal imaging, diabetic retinopathy screening, including diabetes education, at baseline, followed by lifestyle assessment six months later, including self-management support. An electronic CVD and diabetes decision support tool that includes an Indigenous-specific CVD risk calculator, based on best-practice as generally defined by guidelines in the current Standard Treatment Manual of the Central Australian Rural Practitioner’s Association [CARPA], will be developed in conjunction with a clinical working group and used to generate a clinical recommendations report to assist clinicians with evidence-based management of CVD, diabetes and diabetic retinopathy approximately 6–18 months after baseline. Mobile tablet technology based on clinical input and feedback will be developed to support clinical staff and participants with engagement in diabetes management and self-management, respectively.

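### The stated minimum of 490, attrition of 25% and enrolment target of 600 do not fit together

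*Protocol article*

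**What the plan says.** The Sample Size section of the protocol article has three sentences. The first sets the requirement: "For a conservative differential in adherence to subsequent care of 15%, and with 80% power, the minimum sample required is 490". The second and third give the allowance for losses and the resulting target: "Estimates are based on a 25% attrition rate. We will therefore need 600 participants across the three partner sites".

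The target of 600 also appears in the abstract, under Study design and at the end of Data analysis, where 576 participants are reported as already recruited. None of these places explains how 600 was reached. Study design describes the trial in these words: "This is a pre-post study of technology-facilitated management of diabetes, CVD, and diabetic retinopathy". Data analysis sets alpha at 0.05 with 95% confidence intervals.

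**The concern.** The third sentence is worded as a consequence of the first two, so a reader will take 600 to be 490 enlarged for a 25% loss. It is not. A required number, a loss rate and an enrolment target are tied by one equation, and here any two of the three contradict the third.

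This is the only justification the article gives for the size of the trial. If the figures stand as printed, a reader cannot tell how many evaluable participants the plan counts on, or what power goes with that number. A modest or null result on adherence could not then be set against the planned sensitivity.

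**Working it through.** **Inputs.** Minimum sample 490, power 80%, attrition 25% and enrolment target 600 (all Sample Size); recruited so far 576 and alpha 0.05 (Data analysis). A two-sided test is assumed, in keeping with the 95% intervals.

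**1. Trying to reproduce 600.**
- Correct inflation, N/(1 − d): 490/0.75 = 653.3, so 654. This is 54 above 600.
- Common mistaken inflation, N × (1 + d): 490 × 1.25 = 612.5. This is within about 2% of 600, so a rounded use of the wrong formula is a plausible source, but the article does not say so.

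**2. What 600 delivers.**
- Remaining after 25% loss: 600 × 0.75 = 450, short of 490 by 40 (40/490 = 8.2%).
- Attrition at which 600 still leaves 490: 1 − 490/600 = 18.3%.
- The 576 recruited so far would leave 576 × 0.75 = 432.

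**3. Power, if 490 means completers.** Assume that 490 completers give exactly 80% power. The standardised effect at 490 is then 1.96 + 0.84 = 2.80, and it scales with the square root of the sample size:
- At 450: Φ(2.80 × √(450/490) − 1.96) = 76.6%.
- At 432: Φ(2.80 × √(432/490) − 1.96) = 74.9%.

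**4. Power, if 490 already includes the losses.** The evaluable number needed is then 490 × 0.75 = 367.5. Enrolling 600 leaves 450, which exceeds it. By the same scaling, power is Φ(2.80 × √(450/367.5) − 1.96), or about 87%. But 490 would then itself be the enrolment figure, and nothing stated raises it to 600.

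**5. Can the section's figures tell these two readings apart?** They cannot.
- *Absolute 15-point difference, two independent groups, 80% power.* Over lower rates from 5% to 80% in steps of 5 points, the largest total is 346, or 372 with continuity correction. With the correction and lower rates of 35% to 50%, the totals are 366 to 372. Dividing by 0.75 gives 488 to 496, so 490 could be a figure that already contains attrition.
- *Absolute 15-point change, paired (McNemar).* The number of pairs depends on the share of participants whose status changes: 173 at 50% discordance, 242 at 70% and 347 at the limit of 100%. All are below 490.
- *Relative 15% difference, two independent groups.* A baseline near 71% needs about 498 in total and one of 72% about 468, so 490 can also be reached as a completer count.

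**The case against.** The best defence is that the sentence on attrition directly follows the 490, so 490 may be the figure that already carries the 25%. Step 4 shows that 600 is then more than enough. This stands as a possibility, and it is why no unconditional loss of power can be claimed. It does not rescue the text, because the step from 490 to 600 would then have no stated basis.

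A second defence is that 450 is a complete-case figure. Visits and hospitalisations come from electronic health records, and Data analysis plans multiple imputation and a multilevel model alongside complete-case analysis. Attrition of 25% therefore need not remove 25% of the primary-outcome data. This is fair and may soften the practical effect, but it does not change how the three printed numbers relate to each other.

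A reader might infer three stronger things that the document does not support:
- *That the trial is underpowered.* The 76.6% depends on 490 being a completer count. For an absolute 15-point difference between two independent groups, 450 in total would give about 89% power even at the least favourable rates.
- *That 490 is itself wrong.* It does not reproduce as a completer count for an absolute 15 points, but it does for a relative 15% from a baseline near 71% to 72%.
- *That the missing baseline rate, test, discordance and absolute-or-relative definition are faults.* A journal article commonly leaves these to the full protocol or analysis plan, which are not shown.

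**Conclusion.** The point holds as an inconsistency among three printed figures. With a minimum of 490 and 25% attrition the target should be 654. With a target of 600, either 450 are expected to remain or the tolerable attrition is 18.3%. This needs no assumption beyond reading the three sentences together, and nothing elsewhere in the article reconciles them.

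The effect on power is conditional. If 490 completers give exactly 80%, the loss at 450 is about 3.4 percentage points (80% to 76.6%). If 490 already includes attrition, there is no loss. The article does not let a reader choose between the two. The sample-size statement therefore has to be corrected, but this is no evidence that the trial is too small.

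**What to change.** Keep 600, and restate the Sample Size section so that its figures agree:

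1. Say whether 490 is the number before or after attrition.
2. If it is the number of completers needed, do one of two things. Either state that 600 tolerates about 18% attrition, or keep 25% and state the power or detectable difference at 450 evaluable, calculated for the pre-post comparison the trial will make.
3. If 490 already includes attrition, say so and give the separate reason for 600.

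The cost is a few sentences and one recalculation. No extra participants are needed. The only downside is that the restated figure may be slightly less favourable than 80% power at 25% attrition.
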